# Adverse Events and Serious Adverse Events

## Definition of Adverse Event

An adverse event (AE) is defined as any untoward medical occurrence associated with the use of an intervention in humans, whether or not considered intervention related.

## Definition of Serious Adverse Event

An AE that results in any of the following outcomes is defined as a Serious Adverse Event:

- Death,
- Life-threatening adverse experience*,
- Inpatient hospitalization or prolongation of existing hospitalization,
- Persistent or significant disability/incapacity,
- Congenital anomaly/birth defect, or cancer, or
- Any other experience that suggests a significant hazard, contraindication, side effect or precaution that may require medical or surgical intervention to prevent one of the outcomes listed above,
- Event that changes the risk/benefit ratio of the study.

*A life-threatening adverse experience is any AE that places the patient or subject, in the view of the investigator, at immediate risk of death from the reaction as it occurred, i.e., it does not include a reaction that, had it occurred in a more severe form, might have caused death.

## Classification of Adverse Events

### Severity

Adverse events are graded according to the Common Terminology Criteria for Adverse Events (CTCAE) as developed and revised by the Common Therapy Evaluation Program (CTEP) of the National Cancer Institute.

### Attribution

Adverse events are further given an assignment of attribution or relationship to study intervention or procedure. Attribution categories are:

- **Definite** – The adverse event is clearly related to the study intervention or procedure.
- **Probable** – The adverse event is likely related to the study intervention or procedure.
- **Possible** – The adverse event may be related to the study intervention or procedure.
- **Unrelated** – the adverse event is clearly not related to the study intervention or procedure.

### Expectedness

An adverse event is considered unexpected if it is not listed in the investigator brochure or package insert(s), or is not listed at the specificity or severity that has been observed, or, if an investigator brochure is not required or available, the event is not consistent with the risk information described in the general investigational plan or elsewhere in the current application.

## Adverse Events Monitoring

This study is a minimal risk level study that does not require monitoring by the HDFCCC Data and Safety Monitoring Committee (DSMC) as per the National Cancer Institute-approved Data and Safety Monitoring Plan. Ultimately, the PI is responsible for the safety and conduct of this study.

## Follow up of Adverse Events

All participants who experience adverse events will be followed with appropriate medical management until resolved or stabilized, as determined by the investigator.

## Documenting and Reporting of Adverse Events

Adverse Events will be documented in the study Case Report Forms (CRFs) and reported to the IRB, HDFCCC DSMC, and collaborators in accordance with all applicable institutional and regulatory requirements.

# Statistical Considerations

## Sample Size Considerations

### Sample Size and Power Estimate

Because pilot studies are too small to definitively test hypotheses or estimate precise

effect sizes, we do not provide power analyses. As the primary aim of this pilot study is to assess feasibility and acceptability of the research protocol for a future clinical trial, the sample size of *N*=90 (45 in each condition) was set primarily for practical reasons and not driven by hypothesis testing or estimating precise effect size estimates. Effect sizes used to inform power analysis for a future full-scale RCT will be based on clinically important differences in primary abstinence outcomes.

### Randomization and Blinding

See Section 4.6

### Stratification Factors

Not applicable.

### Accrual Estimates

We will recruit all participants by 1 year.

## Interim Analyses and Stopping Rules

Not applicable

## Statistical Analysis Plans

1. ***Statistical analyses****.* Because pilot studies are too small to definitively test hypotheses or estimate precise effect sizes, we do not propose any inferential statistics. Primary analyses will include descriptive statistics of the feasibility and acceptability indicators, comparing each statistic (e.g., % retained) to its tabled threshold (above, see Section 5.2). Above-threshold findings will suggest a reasonable level of feasibility and acceptability for the corresponding aspects of study procedures. Any sub-threshold finding would suggest that remedial modifications to study procedures and/or design would be required prior to moving forward with a full-scale RCT. We also will examine descriptive statistics of the primary and secondary clinical outcomes and include exploratory analyses of relevant biological variables such as age, sex, and race/ethnicity. To the extent possible, descriptive anaylses will consider whether feasibility and acceptability outcomes were consistent across service providers and service settings.

.

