**Intervention.** In addition to receiving usual cessation care, CM intervention participants with CO-verified abstinence will obtain a CM incentive payment, via gift cards redeemable in national retail chains, according to a pre-defined schedule. Gift card amounts and assessment frequencies are based on prior studies among individuals experiencing homelessness or with substance use disorders,^26,30,32,33,38^ and are expected to be effective in promoting smoking cessation. We think this CM schedule is close to what will be adopted; however, our results from Aim 1 will inform the protocol. Gift card amounts will begin at US $13 and increase by $0.50 for each negative CO specimen throughout the first 6 months of the program to a maximum of $24.50 per specimen for a total of 25 specimens collected through week 24 (Table 3). An escalating schedule that increases per visit incentive payment over time is especially important in this study to maintain motivation as visit frequency decreases over time. The total amount that participants can earn under the contingent incentive program through week 24 is $620, an amount comparable to what has been used in prior studies.^30-33^ Test results indicative of smoking (i.e. CO >5ppm) or missed visits will lead to resetting the gift card amount back to the initial low value, but two consecutive negative tests will restore the value back to the highest level previously achieved. ^26,30,32,33,100^

**Control condition.** Control group participants will receive a fixed amount of $5 for attending each abstinence assessment visit and participate in usual cessation care, as described above.^32^ This approach has been used in a prior study of CM for smoking cessation among homeless adults.^32^

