## Adherence Assessment

Using a combination of qualitative and quantitative methods, we will evaluate whether: 1) we met our screening and recruitment goals, 2) the randomization scheme worked and that participants were willing to be randomized, 3) the CM intervention was delivered with fidelity, 4) the retention procedures enabled tracking and retention, 5) the outcome assessments were valid, reliable, and complete, and 6) participants adhered to the protocol (Table 2).

| **Table 2: Feasibility and acceptability outcomes** | | |
| --- | --- | --- |
| Outcomes | **Measure** | **Threshold** |
| Screening | # opting out, # screened | 40 screened per month |
| Recruitment | # enrolled per month | 8/month for 12 months |
| Randomization | Proportion enrolled who are randomized | 90% randomized to intervention and control arms^32^ |
| Fidelity | Observations of incentive payment delivery | Incentive payments that are due are delivered within 2 days of the visit by study staff |
| Adherence | Protocol adherence to the CO assessment schedule  Attendance to counseling sessions  Adherence to NRT among those prescribed NRT | 75% of those enrolled will provide a CO sample at 60%-70%, i.e., 14 -17 out of 25 possible assessment visits^32,33^  75% will attend at least 6 out of 12 counseling sessions during the treatment duration^33^  75% will adhere to using NRT for at least half of the treatment duration^33^ |
| Retention | Proportion of the sample retained as a result of retention procedures | 2 weeks (85%), 3-month (85%), 6-month (75%), and 1 year (75%) retention rates |
| Assessment | Proportion who completed all questionnaires | 75% completed all questionnaires |
| Acceptability | Questionnaire and qualitative interviews with staff and patients | 75% satisfied with the overall intervention |

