## Lost to Follow-up

A participant will be considered lost to follow-up if he or she fails to return for a scheduled visits and study staff are unable to contact the participant after at least 3 attempts. Before a participant is deemed lost to follow-up, the investigator or designee will make every effort to regain contact with the participant (where possible, 3 telephone calls and, if necessary, a letter to the participant’s last known mailing address or local equivalent methods). These contact attempts will be documented in the participant’s study file. Should the participant continue to be unreachable, he or she will be considered to have withdrawn from the study with a primary reason of lost to follow-up.

Participants will be asked to provide and update contact information at each visit. If a participant does not present for their scheduled visit, study staff will call the participants, or contact the participant’s contacts, or visit the places the participant reported that they spend time. Between the 6 month and 12 month assessment, participants will be asked and incentivized to check-in monthly by phone or in-person. We will hire two people who will assist with recruitment and retention efforts – patients seeking care at the TWUHC, RFPC, or PHP who have experienced homelessness and not participating in the trial – who will assist in contacting participants who are lost to follow-up.^52,53^ We have used these tracking procedures successfully in prior studies that have had a similar frequency of visits and length of follow-up.^61-63,65-69^ Based on prior work, we expect retention rates of 85% at 2 weeks, 85% at 3 months, and over 75% at 6-months and 1-year follow-up.^61-63,65-69^

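### The all-questionnaires threshold equals the most that 75% late retention allows, and the retention cut-offs sit at or on the floor of the forecast, so a pilot running as forecast would often be flagged sub-threshold

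*Protocol*

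**What the plan says.** Section 9.3 (Statistical Analysis Plans) makes the comparison of each feasibility and acceptability statistic with its tabled threshold the primary analysis. A pass is read row by row: "Above-threshold findings will suggest a reasonable level of feasibility and acceptability for the corresponding aspects of study procedures". A shortfall on any row has a stated consequence: "Any sub-threshold finding would suggest that remedial modifications to study procedures and/or design would be required prior to moving forward with a full-scale RCT". No interval or test goes with the comparison ("we do not propose any inferential statistics"), and Section 9.1.1 adds "we do not provide power analyses".

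Table 2, under Adherence Assessment, sets the Retention row at "2 weeks (85%), 3-month (85%), 6-month (75%), and 1 year (75%) retention rates" and the Assessment row at "75% completed all questionnaires". The Assessment row gives no denominator. Structured questionnaires fall at enrolment, 2 weeks, and 1, 3, 6 and 12 months (Section 3.1), so all means six occasions.

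The forecast is in Lost to Follow-up (Section 5.7): "we expect retention rates of 85% at 2 weeks, 85% at 3 months, and over 75% at 6-months and 1-year follow-up". No forecast or threshold is given for retention at 1 month.

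On payment, Section 5.1 says: "Control group participants will receive a fixed amount of $5 for attending each abstinence assessment visit". In the intervention arm, payment at those visits depends on CO-verified abstinence. Questionnaire payments, and the check-in payment between 6 and 12 months, are the same in both arms.

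**The concern.** A feasibility threshold should separate a pilot that went as planned from one that did not. Here the cut-offs lie at the forecast or at its lower edge, the comparison is a point estimate on 90 people, and one shortfall is enough to suggest modification. The all-questionnaires row also counts attrition a second time, because anyone lost before 12 months fails it automatically.

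The investigators could be told to change procedures when nothing went wrong. A real shortfall would look the same as sampling noise.

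The consistency check in Section 9.3 names providers and settings but not arms. A pooled rate can hide a gap between arms: 68/90 could be 41/45 (91%) and 27/45 (60%). That split is only an illustration and the protocol does not forecast it.

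**Working it through.** **Inputs.** N = 90, 45 per arm (Section 4.6). Retention thresholds are 85/85/75/75% and the Assessment threshold is 75% (Table 2). Forecast retention is 85%, 85%, then above 75% at 6 and 12 months (Section 5.7). Assumptions: 1-month attendance 85%; late retention 75% (the floor) or 80%; the Assessment denominator is everyone enrolled. The protocol derives no threshold by formula, so there is no figure of its own to reproduce.

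**Cut-offs in people.** 0.85 × 90 = 76.5, so 77 are needed. 0.75 × 90 = 67.5, so 68 are needed. An exact tie cannot occur at N = 90.

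**Ceiling for completing all questionnaires.** The proportion present every time is at most the smallest single-visit proportion:
- Upper bound: min(0.85, 0.85, 0.85, 0.75, 0.75) = 75%, which equals the threshold. With late retention at 80%, the bound is 80%.
- Independent misses: 0.85³ × 0.75² = 0.345, or 35%. With 80% late: 0.85³ × 0.80² = 0.393, or 39%.
- Nested dropout (nobody misses and returns), with 95% of those retained completing everything: 0.75 × 0.95 = 71.3%, and P(X ≥ 68 | 90, 0.7125) = 22%. With 80% late: 0.80 × 0.95 = 76%, and P = 60%.

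**Retention rows singly (binomial, n = 90).**
- P(X ≥ 77 | 0.85) = 51.4%
- P(X ≥ 68 | 0.75) = 50.8%
- P(X ≥ 68 | 0.80) = 88.0%

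**At least one sub-threshold row among the four retention rows and the questionnaire row.** Under nested dropout, X₃ ~ Bin(90, 0.85) is the number present through 3 months, and X₁₂ | X₃ ~ Bin(X₃, q/0.85) the number present at both 6 and 12 months. With full completion among those retained, all five rows pass when X₃ ≥ 77 and X₁₂ ≥ 68. The intermittent cases come from a simulation with an exchangeable latent correlation between visits (20,000 runs).

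| Attendance pattern | Late retention 75% | Late retention 80% |
|---|---|---|
| Nested, everyone retained completes all | 61% | 49% |
| Nested, 95% of those retained complete all | 81% | 56% |
| Intermittent, latent correlation 0.9 | 93% | 79% |
| Intermittent, latent correlation 0.7 | 99.9% | 99% |

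Higher late retention cannot bring the first row much below 49%, because the 85% cut-offs alone fail with probability 1 − 0.514 = 48.6%.

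**Size of the noise.** The 95% Wilson interval for 68/90 (75.6%) is 66% to 83%.

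**Candidate replacement row.** Follow-up questionnaires completed out of those due, at forecast: (0.85 + 0.85 + 0.85 + 0.75 + 0.75)/5 = 81%. If baseline were counted as 100%, a 75% threshold would pass with late completion of only (6 × 0.75 − 1 − 3 × 0.85)/2 = 47.5%. Without baseline it passes at (5 × 0.75 − 3 × 0.85)/2 = 60%, so the late retention rows must stay as separate criteria.

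**The case against.** The strongest reply is that this is a deliberately descriptive pilot. Section 9.3 reads each row for its own aspect of the procedures, and a shortfall suggests remedial modification, which may be small. Nothing is declared a failure overall, and the rows are read together with staff notes and interviews. That stands: a reader might infer a go/no-go rule, and the text does not support one.

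Three other strong readings also go too far.
- A reader might infer that the questionnaire threshold exceeds what forecast retention allows. It equals the maximum at 75% late retention, and the forecast is above 75%, so the row can be met.
- A reader might infer that a pilot on forecast is almost certain to be flagged. That depends on how a participant's missed visits are correlated, which the protocol does not state. Treating unreachable participants as withdrawn points towards nested dropout; active tracing of lost participants points towards people missing visits and returning.
- A reader might infer that a participant in the intervention arm who smokes is paid nothing for attending. Section 5.1 pays everyone for the questionnaires at every retention time point. The difference between arms concerns CO visits through month 6.

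The Assessment denominator is also unstated. If it means those retained, the ceiling argument lapses. A statistical analysis plan might settle denominators, intervals and tables by arm. It would not undo thresholds and a decision sentence that the protocol already fixes.

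**Conclusion.** The point holds in a limited form. If the Assessment row is taken over those enrolled, its 75% threshold is the ceiling set by 75% late retention and has no room for an intermittent miss. The 2-week and 3-month retention cut-offs equal the forecast, and the 6- and 12-month cut-offs are its floor.

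Because any single row can prompt modification on a point estimate, performance exactly as forecast is flagged about half the time or somewhat more (49% to 61%) in the most favourable case. The chance rises with intermittent misses or incomplete questionnaires. These figures rest on N = 90, late retention between 75% and 80%, and, where misses are not nested, 1-month attendance of 85%.

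The consequence is an unnecessary call for changes to procedures, not abandonment of the full trial. The by-arm point is a lesser one about reporting.

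**What to change.** 1. Restate the Table 2 Assessment row so that it does not count attrition again, and give its denominator. Either use the proportion of follow-up questionnaires due, baseline excluded, that are completed (≥75%; 81% expected at forecast), or use completion among those retained at each time point. The second option needs retained to be defined by something other than completing the questionnaire. Report the proportion completing all six descriptively.
2. Keep 6- and 12-month retention as separate criteria.
3. Show a 95% Wilson interval beside each proportion, and state in Section 9.3 that an estimate below its cut-off whose interval includes the cut-off does not by itself require redesign. A descriptive interval is compatible with doing no hypothesis tests.
4. Report retention, CO provision and questionnaire completion by arm as well as pooled, because payment for CO visits through month 6 differs by arm.

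The cost is wording in Table 2 and Section 9.3 and a few more rows of output, with no new data. The downside is that some rows will be reported as inconclusive. With 90 participants the interval is wide: 60/90 (67%) has an upper limit of 75.5% and would still include a 75% cut-off.

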### Analysis Populations

Not applicable

### Primary Analysis (or Analysis of Primary Endpoints)

We will conduct exploratory analyses to assess feasibility and acceptability of collecting data on primary, secondary and other outcomes.

### Secondary Analysis (or Analysis of Secondary Endpoints)

### Exploratory/Correlative Analysis/Assessments

# Study Management

## Pre-study Documentation

Before initiating this trial, the PI will have written and dated approval from the Institutional Review Board for the protocol, written informed consent form, subject recruitment materials, and any other written information to be provided to participants before any protocol related procedures are performed on any participants.

The PI must comply with GCP/ICH guidelines and all applicable regulatory requirements.

## Institutional Review Board Approval

The protocol, the proposed informed consent form, and all forms of participant-facing materials related to the study (e.g., advertisements used to recruit participants) will be reviewed and approved by the IRB. The initial protocol and all protocol amendments must be approved by the IRB prior to implementation.

## Informed Consent

All participants must be provided a consent form describing the study with sufficient information for each participant to make an informed decision regarding their participation. Participants must sign the IRB-approved informed consent form prior to participation in any study specific procedure. The participant must receive a copy of the signed and dated consent document. The original signed copy of the consent document must be retained in the medical record or research file.

## Changes in the Protocol

Once the protocol has been approved by the IRB, any changes to the protocol must be documented in the form of an amendment. The amendment must be signed by the PI and approved by the IRB prior to implementation.

If it becomes necessary to alter the protocol to eliminate an immediate hazard to participants, an amendment may be implemented prior to IRB approval. In this circumstance, however, the PI must then notify the IRB according to institutional requirements.

*For multicenter studies add:* The Study Chair and the UCSF study team will be responsible for updating any participating sites.

## Case Report Forms (CRFs)

The PI will prepare and maintain adequate and accurate participant case histories with observations and data pertinent to the study. Study specific Case Report Forms (CRFs) will document safety and treatment outcomes for safety monitoring and data analysis. All study data will be entered into OnCore^®^ via standardized CRFs in accordance with the CTMS study calendar, using single data entry with a secure access account. Study personnel will complete the CRFs; the PI will review and approve the completed CRFs.

The information collected on CRFs shall be identical to that appearing in original source documents. Source documents will be found in the participant’s medical records maintained by study personnel. All source documentation should be kept in separate research files for each participant.

In accordance with federal regulations, the PI is responsible for the accuracy and authenticity of all clinical and laboratory data entered onto CRFs. The PI will approve all completed CRFs to attest that the information contained on the CRFs is true and accurate.

The PI will be responsible for ensuring the accurate capture of study data. At study completion, when the CRFs have been declared to be complete and accurate, the database will be locked. Any changes to the data entered into the CRFs after that time can only be made by joint written agreement among the and the trial statistician.

All source documentation and CTMS data will be available for review/monitoring by the UCSF DSMC and regulatory agencies.

## Record Retention

The PI is required to prepare and maintain adequate and accurate case histories that record all observations and other data pertinent to the investigation on each study participant. Study documentation includes all CRFs, data correction forms or queries, source documents, Sponsor-Investigator correspondence, monitoring logs/letters, and regulatory documents (e.g., protocol and amendments, IRB correspondence and approval, signed participant consent forms). Source documents include all recordings of observations or notations of clinical activities and all reports and records necessary for the evaluation and reconstruction of the clinical research study. The PI shall retain records for a period of 2 years following the conclusion of the study.

